|------------------------------|--------------------------------------------------------------------------------------------------------------------------------------------------------------------------------------------------------------------------------------------------------------------------------------------------------------------------------------------------------------------------------------------------------------------------------------------------------------------------------------------------------------------------------------------------------------------------------------------------------------------------------------------------------------------------------------------------------------------------------------------------------------------------------------------------------------------------------------------------------------------------------------------------------------------------------------------------------------------------------------------------------------------------------------------------------------------------------------------------------------------------------------------------------------------------------------------------------------------------------------------------------------------------------------------------------------------------------------------------------------------------------------------|
| Trial name and number | Morphologic changes of the saphenous vein as Y-composite graft based on the left internal thoracic artery versus aortocoronary conduit for coronary artery bypass grafting: A prospective randomized controlled trial (CONFIG trial)
ClinicalTrial.gov 04782492                                                                                                                                                                                                                                                                                                                                                                                                                                                                                                                                                                                                                                                                                                                                                                                                                                                                                                                                                                                                                                                                                                                         |
| Objectives            | This randomized controlled trial is designed to directly compare 1-year morphologic changes of the no-touch saphenous vein as Y-composite (Composite group) versus aortocoronary (Aorta group) grafts in coronary artery bypass grafting (CABG).                                                                                                                                                                                                                                                                                                                                                                                                                                                                                                                                                                                                                                                                                                                                                                                                                                                                                                                                                                                                                                                                                                                                           |
| Design                | Prospective randomized controlled trial                                                                                                                                                                                                                                                                                                                                                                                                                                                                                                                                                                                                                                                                                                                                                                                                                                                                                                                                                                                                                                                                                                                                                                                                                                                                                                                                                    |
| Study periods         | IRB approval date ~ December 31, 2023                                                                                                                                                                                                                                                                                                                                                                                                                                                                                                                                                                                                                                                                                                                                                                                                                                                                                                                                                                                                                                                                                                                                                                                                                                                                                                                                                      |
| Subjects              | Patients who are scheduled to undergo primary isolated CABG                                                                                                                                                                                                                                                                                                                                                                                                                                                                                                                                                                                                                                                                                                                                                                                                                                                                                                                                                                                                                                                                                                                                                                                                                                                                                                                                |
| Sample size           | Total 50 patients                                                                                                                                                                                                                                                                                                                                                                                                                                                                                                                                                                                                                                                                                                                                                                                                                                                                                                                                                                                                                                                                                                                                                                                                                                                                                                                                                                          |
| Methods               | 
Patients over 19 years of age who were scheduled to undergo primary isolated CABG for a multivessel disease on a nonemergency basis and in whom the use of left internal thoracic artery (LITA) and saphenous vein (SV) as bypass conduits was planned were assessed for eligibility for study enrollment. The exclusion criteria included (1) patients undergoing concomitant cardiac procedures including valve or aorta surgery, (2) patients in whom it was not feasible to use the LITA or the SV as a bypass conduit due to intrinsic problems with the vessels, (3) patients with severely atherosclerotic or calcified ascending aorta that precluded the use of aortocoronary anastomosis of the SV, (4) patients who had vasculitis, (5) patients with severe comorbidities that might limit the possibility of 1-year angiographic follow-up and (6) patients who declined to participate in the study.
 
Enrolled patients are randomly assigned to the Y-composite group (the Composite group) or aortocoronary group (the Aorta group) in a 1:1 manner. After surgery, early clinical outcomes and early postoperative angiographic patency are evaluated following the protocol. After discharge, all patients undergo regular postoperative follow-up. At 1 year after surgery, patients are evaluated with coronary angiography and intravascular ultrasound.
 |
| Endpoints             | The primary endpoint of the CONFIG trial was intima-media thickness (IMT) measured by intravascular ultrasound (IVUS) on 1-year angiogram. The secondary endpoints were luminal diameter measured by IVUS on 1-year angiogram, 1-year angiographic graft patency, and clinical outcomes including all-cause mortality, cardiac death, target vessel revascularization, and reintervention at 1 year.                                                                                                                                                                                                                                                                                                                                                                                                                                                                                                                                                                                                                                                                                                                                                                                                                                                                                                                                                                                       |

|                     |                                                                                                                                                                                                                                                                                                 |
|---------------------|-------------------------------------------------------------------------------------------------------------------------------------------------------------------------------------------------------------------------------------------------------------------------------------------------|
| Safety       | Postoperative complications including operative mortality, low cardiac output, bleeding reoperation, perioperative myocardial infarction, perioperative stroke, acute kidney injury, respiratory complications, postoperative atrial fibrillation, and mediastinitis were monitored for safety. |
| Expectations | This trial will provide the difference in the morphologic change of the no-touch SV according to the graft configuration, and help the patients and surgeons to choose optimal graft configuration for long-term patency of SV graft in CABG.                                                   |

# Study Protocol

## 1. Title

Morphologic changes of the saphenous vein as Y-composite graft based on the left internal thoracic artery versus aortocoronary conduit for coronary artery bypass grafting: A prospective randomized controlled trial (CONFIG trial)

## 4. Sponsor

None.

## 5. Funding

None.

## **6. Study period**

IRB approval – December 31, 2023

## **7. Study subjects**

Patients who are scheduled to undergo primary isolated CABG

## **8. Background and Objectives**

### **1) Background**

Revascularization of the left anterior descending artery (LAD) with the left internal thoracic artery (LITA) has been recognized as the standard of care for coronary artery bypass grafting (CABG) because of its excellent long-term patency and survival benefit. However, the grafting strategy for non-LAD target vessels is still controversial. Although many surgeons contend that multiple arterial grafting yields better outcomes than single arterial grafting, multiple arterial grafting is used in only 3.9% to 34.2% of CABG patients in the North America and Europe. In contrast, the saphenous vein (SV) has been the most commonly used conduit for several decades. Although there has been concern regarding the high failure rates of SV grafts in the short- and long-term, recent advances such as novel no-touch (NT) SV harvesting techniques and grafting strategies have shown improved graft patency rates for the SV.

Regarding the grafting strategy of the SV in CABG, previous studies demonstrated favorable graft patency rates and negative remodeling of NT-SV when the SV was used as a Y-composite graft based on the in situ LITA. However, whether the favorable findings for NT-SV composite grafts were due to the effect of using Y-composite grafting or to the NT harvesting technique could not be conclusively determined because these two modifications were adopted at the same time during the study period; no study has directly compared the results of SV grafts harvested using the same technique but different grafting strategies.

A randomized controlled trial entitled as 'Morphologic Changes Of the No-touch saphenous vein as Y-composite versus aortocoronary graFts In coronary artery bypass Grafting(CONFIG)' is designed to compare the 1-year morphologic features of NT-SV used as Y-composite grafts based on the in situ LITA with those of NT-SV used as aortocoronary grafts.

### **2) Hypothesis and Objectives**

The present study is conducted to compare the 1-year morphologic features of NT-SV used as Y-composite grafts based on the in situ LITA with those of NT-SV used as aorto-coronary

grafts.

We hypothesize that the intima-media thickness (IMT) of the SV from aortocoronary configuration is higher than that of the SV from Y-composite configuration at 1-year angiographic follow-up and IVUS study.

## **9. Inclusion criteria, Exclusion criteria and Sample size calculation**

### **1) Inclusion criteria**

- ① Patients who are scheduled to undergo primary isolated CABG for a multivessel disease
- ② Patients over 19 years of age
- ③ Patients who are planned to use of LITA and SV as bypass conduits
- ④ Patients who or whose legal representative fill out a written consent form before the start of the clinical trial and patients who can comply with the clinical trial requirements

### **2) Exclusion criteria**

- ① Patients with concomitant cardiac procedures including valve or aorta surgery
- ② Patients in whom it is not feasible to use the LITA or the SV as a bypass conduit due to intrinsic problems with the vessels
- ③ Patients with severely atherosclerotic or calcified ascending aorta that precludes the use of aortocoronary anastomosis of the SV
- ④ Patients who have vasculitis
- ⑤ Patients with severe comorbidities that may limit the possibility of 1-year angiographic follow-up
- ⑥ Patients who refused study enrollment

### **3) Sample size calculation**

Based on previous studies, the reference IMT was estimated;  $0.31 \pm 0.12$  mm for the Y-composite configuration and  $0.43 \pm 0.09$  mm for the aortocoronary configuration. The study was designed to have 90% power to detect a significant difference in IMT between the 2 groups with a 2-sided type I error of 5.0%. Based on this power calculation, 17 patients were needed in each group. Allowing for a 30% dropout rate during the 1-year follow-up, recruitment of 50 patients (25 patients in each group) was determined to be necessary.

(1) Level of significance ( $\alpha$ ) = 0.05

(2) Type II error ( $\beta$ ) = 0.10, power of the test = 90%

(3) Drop out rate = 30%

(4) Two-tailed test

**H0(null hypothesis):  $\mu_1 = \mu_2$**

**H1(alternative hypothesis):  $\mu_1 \neq \mu_2$**

( $\mu_1$ : mean IMT of SV graft of the study group on 1 – year IVUS,

$\mu_2$ : mean IMT of SV graft of the control group on 1 – year IVUS )

The calculation was performed using PASS Software(Power Analysis and sample size software: <http://www.ncss.com>), and the calculated formula is as follows.

$$n = \frac{\left( Z_{\frac{\alpha}{2}} + Z_{\beta} \right)^2 (\sigma_1^2 + \sigma_2^2)}{(\mu_1 - \mu_2)^2}$$

$\mu_1$  = mean IMT of SV graft in the study group on 1 – year IVUS

$\mu_2$  = mean IMT of SV graft in the control group on 1 – year IVUS

$\sigma_1$  = standard deviation of IMT of SV graft in the study group on 1 – year IVUS

$\sigma_2$  = standard deviation of IMT of SV graft in the control group on 1 – year IVUS

#### 4) Subject recruitment plan

Subject recruitment will be performed for the patients who are scheduled to undergo isolated primary CABG and who are hospitalized at Seoul National University Hospital I after providing sufficient explanation and informed consents.

## 10. Methods

### 1) Detailed process of the study

Patients over 19 years of age who were scheduled to undergo primary isolated CABG for a multivessel disease on a nonemergency basis and in whom the use of LITA and SV as bypass conduits was planned were assessed for eligibility for study enrollment. After excluding the patients who meet the exclusion criteria and who refuse to participate, enrolled patients are randomly assigned to 1 of the 2 configurations in a 1:1 manner.

#### Operative strategies and Randomization process

Surgeries will be performed under standard median sternotomy, and off-pump CABG (OPCAB) will be the preferred grafting strategy during the study period. The in situ LITA will be

harvested using the skeletonization technique. The SV will be simultaneously harvested, preferentially from the lower leg, using a NT technique that retains perivascular soft tissue as previously described. Randomization will be performed after the conduits are harvested without injury and it is confirmed that the intraoperative findings indicate that either of the grafting strategies are feasible. Web-based block randomization will be performed using randomly determined block sizes of 4 and 6. After randomization, the procedures will be performed according to the assigned grafting strategy. In the patients assigned to the Composite group, the Y-composite graft is constructed first by anastomosis of the distal end of the SV graft to the side of the LITA, and anastomosis of the LITA to the LAD territory is performed whenever necessary. The SV is then anastomosed to the diagonal branch, to the vessels in the left circumflex coronary artery(LCX) territory, and then to the vessels in the right coronary artery(RCA) territory as needed using a sequential anastomotic technique. In the patients assigned to the Aorta group, the SV is first anastomosed to the ascending aorta using the Heartstring III Proximal Seal System (MAQUET Holding B.V. & Co. KG, Rastatt, Germany). The LITA is then anastomosed to the target vessel in the LAD territory. Finally, the SV is anastomosed sequentially to the diagonal branch, to the vessels in the LCX territory and then to the vessels in the RCA territory as needed using a sequential anastomotic technique.

※ Randomization : Patients who meet the inclusion criteria and the exclusion criteria are randomly assigned to 1 of the 2 configurations in a 1:1 manner. Randomization is performed with a web-based block randomization method (<https://mrcc.snuh.org/>) with randomly determined block sizes of 4 and 6.

### **Histologic evaluation of the saphenous vein**

Immediately after harvesting, the distal end of the SV, approximately 2mm in length, will be sampled and preserved as formalin-fixed paraffin-embedded tissue for histologic evaluation. The histologic evaluation is designed to compare the intima-media thickness (IMT) of the SV in the 2 groups as a baseline value of the IMT and as an indicator of the quality of the SV. The specimen will be divided into 3 sections perpendicular to the vessel lumen. Histologic evaluation will be performed using hematoxylin and eosin staining and Masson's trichrome staining. The IMT will be measured in 4 directions for each section, and the values obtained for the 3 sections will be averaged.

### **Postoperative process and follow-up plan**

Patients are evaluated with early clinical outcomes and early postoperative angiographic measurements. After discharge, all patients undergo regular postoperative follow-up through the outpatient clinic at 3- to 6-month intervals and are interviewed by telephone for confirmation of their condition if the last clinic visit has not been conducted as scheduled. At postoperative 1-year, clinical outcomes and angiographic measurements are evaluated as scheduled. The measurement of IMT using IVUS will be simultaneously performed during 1-year angiographic evaluation.

### **Intravascular ultrasonographic (IVUS) study**

The IVUS study will be performed after the completion of 1-year postoperative angiography in a standard fashion using an automated motorized pullback system (0.5 mm/s) with commercially available imaging catheters (Boston Scientific/SCIMED, Minneapolis, Minnesota, USA). The IVUS images will be acquired after the administration of 100 to 200 mg of nitroglycerin. In case of Y-composite grafting, the IVUS catheter will be advanced into the SV conduit connected to the mid-portion of the LITA and located at around 5 cm distal to the Y-anastomosis, and a pullback will be performed for the total length of 10 cm. To avoid the influence of suture materials, the areas 1 cm proximal and distal from the Y-anastomosis will be excluded from the analysis. In case of aortocoronary grafting, the IVUS catheter will be advanced into the SV conduit and located at around 5 cm distal to the aortocoronary anastomosis, and a pullback will be performed for the total length of 5 cm. The IVUS catheter will be also advanced into the LITA conduit and located at around 15 cm distal to the subclavian arterial origin, and an automated motorized pullback will be performed for the total length of 10 cm. To be a reference to the Y-composite group, the areas 1 cm distal from the aortocoronary anastomosis and the middle 2cm of evaluated LITA will be excluded from the analysis. The IVUS analysis will be performed by 1 independent experienced observer. Quantitative analyses of the IVUS data will be performed using computerized planimetry software (echoPlaque 3.0, Indec Systems Inc, Santa Clara, California, USA).

The lumen and vessel areas will be measured every 1 millimeter. All volumes will be calculated using the Simpson rule and then normalized for analyzed length. The area of intima-media (IM) will be calculated by subtracting the luminal area from the vessel area. The proportion of IM area to vessel area will be also calculated.

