## **2) Outcome measures**

- 1) Demographics: age, sex, height, weight, body mass index, body surface area, diagnosis,

operation name

2) Preoperative data

- Risk factors: diabetes mellitus, hypertension, smoking, dyslipidemia, stroke, chronic obstructive pulmonary disease, chronic kidney disease, chronic liver disease, coronary disease, peripheral vascular disease, history of cardiac surgery, New York Heart Association functional class, STS mortality risk, EuroSCORE II, SYNTAX score
- Electrocardiography
- Pulmonary function test
- Laboratory tests
- Echocardiographic measurements: LV ejection fraction, LV end diastolic dimension, LV end systolic dimension, regional wall motion abnormalities, etc.
- Coronary angiography : 1-vessel disease/2-vessel disease/3-vessel disease/left main disease, degree of stenosis for each branch

3) Operative data: number of anastomoses, target vessels, location of anastomosis, operative findings

4) Postoperative data

- Early clinical outcomes: op mortality, op morbidities (low cardiac output, bleeding reoperation, perioperative myocardial infarction, perioperative stroke, acute kidney injury, respiratory complications, postoperative atrial fibrillation, and mediastinitis)
- Echocardiographic measurements: LV ejection fraction, LV end diastolic dimension, LV end systolic dimension, regional wall motion abnormalities, etc.
- Coronary angiography : patency of bypass grafts, patency of distal anastomoses, presence of competitive flows for each anastomosis

5) 1-year follow-up data

- Clinical outcomes: all-cause mortality, cardiac mortality, major adverse cardiac events, reintervention, target vessel revascularization
- Echocardiographic measurements: LV ejection fraction, LV end diastolic dimension, LV end systolic dimension, regional wall motion abnormalities, etc.
- Coronary angiography : patency of bypass grafts, patency of distal anastomoses, presence of competitive flows for each anastomosis
- Intravascular ultrasound (IVUS) : intima-media thickness (IMT), lumen diameter (LD)

※ Primary clinical endpoint

Intima-media thickness (IMT) measured by IVUS on 1-year angiogram

※ Secondary clinical endpoint

Luminal diameter measured by IVUS on 1-year angiogram

One-year angiographic graft patency

Clinical outcomes including all-cause mortality, cardiac death, target vessel revascularization, and reintervention at 1 year

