## **8) Schedules**

- ① Study planning : March 1, 2021 – June 30, 2021
- ② Enrollment : July 8, 2021 – October 26, 2022
- ③ Data analysis and reporting : January 1, 2023 – December 31, 2023

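### The nitroglycerin dose before the 1-year IVUS is given in milligrams; micrograms were very probably meant, and the unit should be confirmed in the source protocol

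*Protocol*

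**What the plan says.** The dose appears once, in the Protocol's section 10, subsection on the IVUS study: "The IVUS images will be acquired after the administration of 100 to 200 mg of nitroglycerin". No route, maximum dose or reference is given, and the drug is not mentioned anywhere else.

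The instruction belongs to the visit at which the primary endpoint is measured. The follow-up plan states: "The measurement of IMT using IVUS will be simultaneously performed during 1-year angiographic evaluation". The outcome list names the primary endpoint as "Intima-media thickness (IMT) measured by IVUS on 1-year angiogram", and luminal diameter from the same IVUS is a secondary endpoint.

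The IVUS subsection opens with a general statement of how the examination is done: "The IVUS study will be performed after the completion of 1-year postoperative angiography in a standard fashion". The dose sentence comes before the text splits into separate catheter instructions for the two configurations, so it applies to both arms.

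**The concern.** A dose of 100 to 200 mg of nitroglycerin is not plausible as a single dose of a vasodilator before imaging. The numerals fit a dose in micrograms, which suggests a slip in the unit rather than a choice made on purpose. Because the drug appears only once, a reader cannot correct the dose from the text itself.

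The sentence tells staff how much of a drug to give, and following it literally would be a gross overdose. What is at stake is patient safety and the accuracy of the written IVUS method, including any later reuse of it. No bias between the arms and no loss of power is claimed.

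**Working it through.** **Inputs.** The dose, 100 to 200 mg, comes from the IVUS subsection. The patient numbers come from the sample size section: "Allowing for a 30% dropout rate during the 1-year follow-up, recruitment of 50 patients (25 patients in each group) was determined to be necessary". The dates come from the schedule, "Enrollment : July 8, 2021 – October 26, 2022", and from section 6, "IRB approval – December 31, 2023". The intended unit (micrograms) is an assumption and is not in the document.

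**Step 1: size of the discrepancy.** The Protocol has no dose calculation to reproduce, so only the unit conversion applies.

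- As written: 100 mg × 1,000 = 100,000 micrograms; 200 mg × 1,000 = 200,000 micrograms.
- If micrograms were meant: 100 / 1,000 = 0.1 mg; 200 / 1,000 = 0.2 mg.
- Ratio: 100,000 / 100 = 200,000 / 200 = 1,000.

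**Step 2: patients covered.**

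- Source reads mg: at most 50 patients, or 50 × (1 − 0.30) = 35 if the dropout allowance is fully used.
- Source already reads micrograms: none.

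**Step 3: when the instruction applies.** Enrollment is taken as the date of surgery, because patients are recruited while in hospital for the operation and randomized during it.

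- First 1-year IVUS: 8 July 2021 + 1 year = 8 July 2022.
- Last 1-year IVUS: 26 October 2022 + 1 year = 26 October 2023, a span of 475 days.
- From 26 October to 31 December 2023, the end of the study period: 66 days.

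On the Protocol's own dates, the imaging is finished before the study period ends.

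**Step 4: effect on the design figures.** The sample size formula uses only means, standard deviations, the error rate and power:

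n = (Z for α/2 + Z for β)² × (σ₁² + σ₂²) / (μ₁ − μ₂)²

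With standard deviations of 0.12 and 0.09 mm, means of 0.31 and 0.43 mm, two-sided α of 0.05 and 90% power:

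n = (1.960 + 1.282)² × (0.0144 + 0.0081) / 0.0144 = 16.42, rounded up to 17 per group.

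17 / (1 − 0.30) = 24.3, rounded up to 25 per group, or 50 in total.

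Both figures agree with the Protocol. The dose does not enter the formula, so correcting the unit leaves them unchanged.

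**The case against.** The strongest objection is that the document may contain no error. The text was read from a PDF by a program, and a micro sign taken for the letter m would give exactly this sentence. The Greek letters and plus-minus signs in the sample size section came through correctly, but they sit in mathematical notation. They are weak evidence of how a micro sign in ordinary prose would fare. This objection stands, and it is why the point is put as a unit to confirm and not as a proven mistake.

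Second, nothing else in the Protocol contradicts the figure, so its implausibility rests on general pharmacology. That is true and is stated as an assumption. The gap is 1,000-fold, however, so the judgment does not depend on which usual dose one takes as the reference.

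Third, the practical effect is small. Staff would very likely give their customary dose, and the imaging window has closed on the stated dates. This also stands and limits the weight of the point. It should be said, though, that the phrase about standard fashion describes how the IVUS examination is performed and does not expressly cover the drug dose.

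Finally, this is not a statistical defect. That is agreed, but a wrong unit in a drug instruction is still worth correcting when it is noticed.

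**Conclusion.** The concern holds as a minor point of dose safety. As shown, the Protocol instructs staff to give an implausible amount of nitroglycerin, 1,000 times the amount very probably intended, at the visit that measures the primary endpoint.

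The conclusion rests on two conditions: that micrograms were meant, which is an assumption, and that the source document prints mg, which cannot be settled from extracted text. If the second fails, nothing needs correcting. Confidence is medium for that reason.

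Since the 1-year visits were due to end by late October 2023, a correction mainly serves the record and anyone who reuses this IVUS method.

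**What to change.** Check the unit in the source protocol and with the treating cardiologists. If it reads mg, replace it with the word micrograms written in full, so that no symbol can be lost in copying, and notify the ethics committee. If the source already reads micrograms, no change is needed.

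The cost is one word and, if the source reads mg, one notification. No additional patients, procedures or staff are required.
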